### **M18 visit = 18 months after randomization +/-15 days**

- Consultation date
- Clinical examination: weight, blood pressure, edema
- Serious adverse events
- Changes in concomitant treatments
- Blood and urine lab results
- Estimated GFR CKD EPI
- Check remission status:
  - Complete clinical remission: urinary protein/creatinine ratio (UPCR) < 0.3 g/g in spot morning urine samples and Normal serum albumin and eGFR > 60 ml/min/1.73 m^2
  - Partial clinical remission: UPCR < 3.5 g/g with a decrease greater than 50% from baseline and improvement or normalization of the serum albumin concentration and increase of serum creatinine lower than 20%
- Centralized assays for both arms:
  - 2 dry tubes of 5 ml of blood and 2 EDTA tubes of 3 ml of blood will be shipped to Nice at room temperature for PLA2R1-Ab, epitope profile determination, B and T cells counts (see manual labPlan visit M24 +/-15 days and hand out a prescription to the patient for blood and urine analyses\*)

\*Blood sample: urea, creatinine, electrolytes (sodium, potassium, chloride, bicarbonate), protein, albumin, full blood count.

Spot morning urine sample: protein, albumin, urea, creatinine.

### **M24 visit = 24 months after randomization +/-15 days**

- Consultation date
- Clinical examination: weight, blood pressure, edema
- Serious adverse events
- Changes in concomitant treatments
- Blood and urine lab results

- Estimated GFR CKD EPI
- Check remission status:
  - Complete clinical remission: urinary protein/creatinine ratio (UPCR) < 0.3 g/g in spot morning urine samples and Normal serum albumin and eGFR > 60 ml/min/1.73 m^2
  - Partial clinical remission: UPCR < 3.5 g/g with a decrease greater than 50% from baseline and improvement or normalization of the serum albumin concentration and increase of serum creatinine lower than 20%
- Centralized assays for both arms:
  - 2 dry tubes of 5 ml of blood and 2 EDTA tubes of 3 ml of blood will be shipped to Nice at room temperature for PLA2R1-Ab, epitope profile determination, B and T cells counts (see manual lab)
- End of study

### **At the first remission**

One tube of lithium heparin of 4 ml of blood (for cytokine profile analysis) will be performed at the first remission and shipped to Nice at 4°C. If the sample cannot be collected during the visit when the remission is first confirmed, it must be collected at the following visit or at M24 for all patients that have not entered remission until the end of study.

### **At the first relapse**

If the patient presents a still active disease with anti-PLA2R1 and anti-rituximab activity, the following cares are left to the investigator's discretion due to the Rituximab contraindication. However, the patient must perform the following visits according to the protocol.

### **8.7 Specimen collection:**

Non-fasted blood samples will be shipped on the same day at room temperature to the Laboratory of Immunology in Nice, overseen by [name] (see instructions in manual lab), except for the tubes of lithium heparin (collected at inclusion and at first remission) that must be immediately stored at 4°C and shipped at 4°C. They will be analyzed and results will be provided to the study site within 48 hours. All samples will be retained after analysis (except if consent for this is withdrawn) to pursue other research goals (they will constitute a collection) and will be stored at -80°C in a secured fridge/freezer located in the Laboratory of Immunology in Nice Hospital. No genetic study

will be performed on the samples. The Nice University Hospital where the collection is stored will be responsible for declaring it to the Research minister and the Agence Régionale d'Hospitalisation. The cell bank has all of the necessary informatic tools and software necessary for conformance with the national bioethical legislation (loi de Bioéthique). The rules governing sample anonymity will be followed.

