***We concluded that:***

- ***early remission rate depends on rituximab dosing,***
- ***low dose of rituximab could be enough for patients with anti-PLA2R1 activity restricted to CysR,***
- ***high dose of rituximab may be required for patients with epitope spreading.***

We will compare two therapeutic strategies in PLA2R1-related iMN patients to induce clinical remission of the nephrotic syndrome at month 12:

1. The strategy validated in the GEMRITUX protocol: 6 months of symptomatic antihypertensive and antiproteinuric therapy, and if the nephrotic syndrome persists at month 6 (UPCR remains > 3.5 g/g and albuminemia < 30 g/l), two 375 mg/m^2 infusions at 1-week interval.

2. A personalized strategy driven by the PLA2R1-Ab epitope profile at month 0 and month 6:

- Patients with restricted anti-CysR activity at month 0: these patients have a spontaneous remission rate under NIAT from 43% to 50% at month-6. We propose a symptomatic antihypertensive and antiproteinuric treatment for 6 months;
- Patients with restricted anti-CysR activity and persisting active disease at month 6 after symptomatic treatment (UPCR remains > 3.5 g/g and albuminemia < 30 g/l): in GEMRITUX, these patients have a high rate of remission with low dose of rituximab (about 70%). We propose two 375 mg/m^2 rituximab infusions at 1-week interval;
- Patients with anti-CTLD1/7 activity at month 0 or month 6 with persisting active disease after symptomatic treatment (UPCR remains > 3.5 g/g and albuminemia < 30 g/l): these patients have a very low rate of spontaneous remission under NIAT (from 0.05% to 17%) or under low dose of rituximab: in GEMRITUX 24% of remission at 6-month vs 64% with high dose of rituximab p=0.04. We propose to treat these patients with high dose of rituximab (two 1g rituximab infusions at 2-week interval at month 0 and/or month 6).

Ruggenti et al. demonstrated on a cohort of 81 consecutive iMN patients with PLA2R1-Ab that PLA2R1-Ab depletion 6 months post-rituximab strongly predicted remission (HR, 7.90; 95% CI, 2.54 to 24.60; P<0.001) (32). We will reevaluate the serologic status of all patients at month-6 and retreat according to the same protocol.

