#### **8.4 Frequency of follow-up visit-protocol**

After randomization, all patients will be scheduled at M3, M6, M9, M12, M18 and M24 post-treatment for a routine follow-up, and benefit from a symptomatic antihypertensive and antiproteinuric treatment throughout the study period according to the KDIGO guidelines.

In the GEMRITUX group: at M6, if the patient exhibits an active disease (UPCR remains  $> 3.5$  g/g and albuminemia  $< 30$  g/l), they will receive two 375 mg/m^2 rituximab infusions at 1-week interval.

In the personalized group, rituximab injections should be scheduled between 5 and 14 days after randomization in case the epitope results are in favor for immunosuppressive treatment, as follows:

- at M0 and M6, if the patient exhibits anti-PLA2R1 anti-CTLD1 or CTLD7 activity, they will receive two 1 g infusions at 2-week interval.
- At M6, if a patient has an active disease/ anti-PLA2R1 ab + or if he has an active disease /anti-PLA2R1 Ab –, symptomatic treatment should be optimized. And if he exhibits anti-CysR restricted activity with active disease (UPCR remains  $> 3.5$  g/g and albuminemia  $< 30$  g/l), they will receive two 375-mg/m^2 rituximab infusions at 1-week interval.

[figure not shown]

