### 8.5 Definition of patient data to be gathered and directly entered in the patient electronic case file, which will be considered the source data:

#### Inclusion/Randomization visit (M0)

- Consultation date
- Demographic data: date of birth, sex
- History of MN
- Paraclinic tests to eliminate secondary MN when performed: body scan, anti-nuclear antibodies, HBV, HCV serologies
- Current treatment
- Clinical examination: weight, height, blood pressure, edema
- Blood sample: urea, creatinine, electrolytes (Na, K, Cl, HCO3), protein, albumin, full blood count
- Urine collection on a spot morning sample: protein, albumin, urea, creatinine
- Centralized assays : for both groups,

- 2 dry tubes of 5 ml of blood and 2 EDTA tubes of 3 ml of blood will be shipped to Nice at room temperature for PLA2R1-Ab, epitope profile determination, anti-rituximab antibodies, B and T cells counts (see manual lab),
  - 1 lithium heparin tube of 4 ml of blood for cytokine profile analysis will be shipped to Nice at 4°C.
- 
- Start vaccination (pneumococcal and influenza vaccine) between randomization and first injection at the latest.
  - In the GEMRITUX arm, plan M3 in 3 months +/-15days and hand out a prescription to the patient for blood and urine analyses\* (results needed for the next visit as per routine follow-up);
  - In the Personalized Treatment arm, plan next visit according to the epitope profile results provided by the central lab within 48 hours:
    - Restricted anti-CysR activity: 6-month symptomatic treatment as in GEMRITUX arm - > plan M3 visit in 3 months +/-15 days and hand out a prescription to the patient for blood and urine analyses\* (results needed for the next visit as per routine follow-up);
    - Anti-CTLD1/7 activity: plan two 1g rituximab infusions at 2-week interval +/-2 days. The treatment should start between 5 and 14 days after randomization. After the first injection, plan M3 visit in 3 months +/-15 days and hand out a prescription to the patient for blood and urine analyses\* (results needed for the next visit as per routine follow-up)

\* Blood sample: urea, creatinine, electrolytes (sodium, potassium, chloride, bicarbonate), protein, albumin, full blood count.

Spot morning urine sample: protein, albumin, urea, creatinine.

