#### **M6 visit = 6 months after randomization +/-15 days**

- Consultation date
- Clinical examination: weight, blood pressure, edema
- Serious adverse events
- Changes in concomitant treatments
- Blood and urine lab results
- Estimated GFR CKD EPI
- Centralized assays for both arms:
  - 2 dry tubes of 5 ml of blood and 2 EDTA tubes of 3 ml of blood will be shipped to Nice at room temperature for PLA2R1-Ab, epitope profile determination, serum rituximab levels, anti-rituximab antibodies, and, B and T cells counts (see manual lab)
- **In the GEMRITUX arm**
  - If disease still active (UPCR remains > 3.5 g/g and albuminemia < 30 g/l): plan two 375 mg/m^2 Rituximab infusions at 1-week interval (+/- 2 days) between 5 and 14 days after M6 visit.
  - If remission (partial or complete, see p.12): symptomatic treatment to be continued.
- **In the personalized arm/ Patients who received RTX at M0**
  - If remission (partial or complete, see p.12): symptomatic treatment to be continued alone and contraception will be required during 12 months after the end of the treatment.
  - If disease still active / Restricted anti-CysR activity: plan two 375 mg/m^2 rituximab infusions at 1-week interval (+/- 2 days) between 5 and 14 days after M6 visit.

- if disease still active / Anti-CTLD1/7 activity: plan two 1g rituximab infusions at 2-week interval (+/- 2 days) between 5 and 14 days after M6 visit. For patient who will develop anti-rituximab antibodies, treatment with human anti-CD20 is widely recommended.

*NB: If the patient still active disease / anti-PLA2R1 Ab-; the symptomatic treatment should be optimized*

- **In the personalized arm/ Patients who received 6-month symptomatic treatment**

- If remission (partial or complete, see p.12): symptomatic treatment to be continued
- If disease still active / Restricted anti-CysR activity: plan two 375 mg/m^2 rituximab infusions at 1-week interval between 5 and 14 days after M6 visit.
- if disease still active / Anti-CTLD1/7 activity: plan two 1g rituximab infusions at 2-week interval between 5 and 14 days after M6 visit.

**For all:** plan M9 +/-15 days and hand out a prescription to the patient for blood and urine analyses\*

\* Blood sample: urea, creatinine, electrolytes (sodium, potassium, chloride, bicarbonate), protein, albumin, full blood count.

Spot morning urine sample: protein, albumin, urea, creatinine.

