#### **10.10 Withdrawal of Study Participants**

The researchers may decide to withdraw the patient from the study if:

- The medical problem becomes worse.
- The researchers believe that participation in the research is no longer safe for the patient.
- The researchers believe that other treatment may be more helpful.
- The sponsor or the EMA stops the research for the safety of the participants.
- The sponsor cancels the research.
- The patient is unable to keep appointments or to follow the researcher's instructions.

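### As written, Section 8.7 releases control-arm epitope profiles to open-label sites whose protocol care never uses them

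*Protocol*

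**What the plan says.** - **Release of results.** Section 8.7, on the samples shipped to the central laboratory: "They will be analyzed and results will be provided to the study site within 48 hours". The sentence names no arm and no assay.
- **What is assayed, and in whom.** At M0 (Section 8.5) the heading is "Centralized assays : for both groups", and the tubes are for "room temperature for PLA2R1-Ab, epitope profile determination, anti-rituximab antibodies, B and T cells counts". At M6 it is "Centralized assays for both arms", again with the epitope profile. The other visits read the same way, and the schedule of assessments marks the profile at all seven visits.
- **Who uses it.** At M0: "In the Personalized Treatment arm, plan next visit according to the epitope profile results provided by the central lab within 48 hours". The GEMRITUX instruction beside it mentions no epitope result. For that arm the M6 decision in Section 8.4 opens "In the GEMRITUX group: at M6, if the patient exhibits an active disease" and rests on UPCR and albumin alone.
- **What investigators are told the result means.** Section 1.2 concludes that epitope spreading at baseline should be considered for early intervention. Section 1.3 says of patients with CTLD1/7 activity and persisting disease: "these patients have a very low rate of spontaneous remission under NIAT (from 0.05% to 17" (the upper end of the range is 17%).
- **Routes for acting on it.** The trial is open label (Section 4). Section 10.10 lists as a ground for withdrawal: "The researchers believe that other treatment may be more helpful".
- **Safeguards.** Section 9.3 prohibits immunosuppressive agents during the study, except to treat a drug-related adverse event. Section 9.1 sends study rituximab after the first randomization only for patients in the personalized arm. Section 12.1 specifies intention to treat, with LOCF for the primary objective.

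**The concern.** The trial asks whether treatment guided by the epitope profile gives more remissions than treatment that ignores it. The comparator stays free of the information under test only if the treating physician does not have it. Section 7.1 puts CTLD1/7 activity at about 70% of patients, so roughly 22 of 32 controls would carry a result that the protocol links to poor remission on symptomatic care.

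A physician who holds that result has two ways to act on it, and they bias the comparison in opposite directions:
- Early off-protocol treatment raises remission in the control arm and dilutes the difference.
- Discretionary withdrawal, followed by LOCF, tends to fix the patient at an early non-remission status and favours the personalized arm.

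Neither can be undone once sites have seen the profiles, and the net direction could not be recovered in the analysis.

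**Working it through.** **1. Does the text release the profile for controls?** Section 8.7 releases results without limit. Section 8.5 and the schedule include the epitope profile for both arms. No other section withholds it. The only place that ties 48-hour release to the epitope profile names the personalized arm (Section 8.5, M0). That suggests an intent to release selectively but does not restrict Section 8.7. So release to control sites follows from the text as written, while the intent is ambiguous.

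**2. Does control care need it?** No. The GEMRITUX decision at M6 uses UPCR and albumin. Other central results are needed in both arms: confirmation of PLA2R1 antibodies (an exclusion criterion in Section 6.2) and anti-rituximab antibodies (Section 6.2 for relapsed patients, and the first-relapse paragraph).

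**3. Baseline power.** Inputs from Sections 7.1 and 7.2: 45% versus 80% remission, 29 per group, 64 in total (32 per arm). The test level is 5% two-sided (Section 12.1). The stated 29 per group reproduces with the uncorrected chi-square formula at 5% (power 80.2%). Exact two-sided Fisher power is 71% at 29 per arm and 78% at 32.

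**4. Illustration of crossover.** The number of crossovers, k, is an assumption; the protocol gives no figure. With base rate b for CTLD1/7 controls and remission rate e after crossover:

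control rate = 0.45 + (k/32) × (e − b)

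Values of b:
- Reading the 50% and 40% in Section 7.1 as additive, CysR-restricted remission is 90%: b = (0.45 − 0.30 × 0.90)/0.70 = 0.257.
- Reading the 40% as applying to the non-remitting half, it is 0.50 + 0.50 × 0.40 = 70%: b = (0.45 − 0.30 × 0.70)/0.70 = 0.343.
- With no difference by epitope: b = 0.45.

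Values of e: 0.85 (Section 7.1, repeated high-dose pulses) and 0.64 (Section 1.3, high dose at six months).

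Four crossovers (12.5% of the arm), Fisher power at 32 per arm against 80%:

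| b | e | Control rate | Power |
|---|---|---|---|
| 0.257 | 0.85 | 52.4% | 57% |
| 0.343 | 0.85 | 51.3% | 60% |
| 0.45 | 0.85 | 50.0% | 64% |
| 0.257 | 0.64 | 49.8% | 65% |
| 0.343 | 0.64 | 48.7% | 68% |
| 0.45 | 0.64 | 47.4% | 72% |

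For example, row one: 0.45 + (4/32) × (0.85 − 0.257) = 0.524. A single crossover gives 74% to 77%.

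**5. Illustration of withdrawal.** If four CTLD1/7 controls are withdrawn while not in remission, LOCF counts all four as non-remitters at M12. The control rate becomes 0.45 − (4/32) × b, which is 41.8%, 40.7% or 39.4% for the three values of b. The movement is opposite to that in step 4.

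**The case against.** The strongest reply has four parts.

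- **Section 8.7 is a general logistics sentence.** Only the personalized arm is linked to a 48-hour epitope result, the laboratory is told the allocation (Section 8.3), and a lab manual that is not shown may already restrict release. This stands as far as intent goes: one should not assert that the laboratory will send control profiles. It does not change what the protocol says.
- **Early rituximab in a control would breach the protocol.** The ban on immunosuppressants and the supply rule stand as real safeguards, and controls with persisting nephrotic syndrome reach rituximab at M6 anyway, so the window for early crossover is about six months. A reader might infer that the protocol permits crossover; it does not. These rules limit crossover without excluding it, and they do not close the withdrawal route in Section 10.10.
- **Intention to treat protects the comparison.** A reader might infer that withdrawn controls drop out of the comparison. Section 12.1 does not support that: they stay in their arm and are imputed by LOCF. But intention to treat does not undo dilution, and LOCF introduces its own tilt.
- **The magnitude is assumed.** This stands. No crossover count has a source, and 57% is the least favourable of the six four-crossover cases, not a forecast.

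A reader might also object to releasing M3, M9 and M12 profiles in the personalized arm. Those physicians are meant to know the profile, and the documents show no harm from it.

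**Conclusion.** The point holds as a gap in the wording that is cheap to close. As written, Section 8.7 gives open-label control physicians the information under test, for no purpose in their arm's care. Whether that is intended is unclear. Crossover and selective withdrawal are foreseeable risks inferred from the design; they are neither permitted outright nor shown to be likely.

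Their size cannot be estimated from the protocol. Four crossovers in 32 would lower Fisher power from 78% to between 57% and 72%. That rests on the assumed count, on the planning rates of 45% and 80%, and on the range of base and benefit rates taken from the protocol's own figures. Withdrawal would push the other way, so no net direction can be claimed.

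**What to change.** In Section 8.7 and the lab manual, state that:
- epitope profiles of GEMRITUX patients are held at the central laboratory and not released to the site at least until M12 remission status is recorded;
- PLA2R1 antibody confirmation and any other result needed for eligibility or safety, such as anti-rituximab antibodies, are still returned in both arms;
- at M0 the profile is released only once the laboratory knows the allocation.

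The last item needs the sequence settled. The Summary ships samples for epitope analysis after consent and randomizes once inclusion criteria are confirmed, whereas Section 8.3 randomizes after consent and then informs the laboratory of the arm. Under the Summary's order the laboratory could report before it knows the arm, so the Summary should be aligned with the release rule.

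The cost is a few sentences and a change to the laboratory's reporting template, with no added assay, visit or patient. The small downside is that control investigators wait for a research result that their arm's protocol does not use.

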### Schedule of assessments

|                                          | M0 | M3                                | M6 | M9 | M12 | M18 | M24 |
|------------------------------------------|----|-----------------------------------|----|----|-----|-----|-----|
| Selection criteria                       | X  |                                   |    |    |     |     |     |
| Informed Consent                         | X  |                                   |    |    |     |     |     |
| Pregnancy test                           | X  | X                                 | X  | X  | X   |     |     |
| Randomisation                            | X  |                                   |    |    |     |     |     |
| Medical history and demographics         | X  |                                   |    |    |     |     |     |
| Weight, Edema, Blood pressure            | X  | X                                 | X  | X  | X   | X   | X   |
| Vaccination                              | X  |                                   |    |    |     |     |     |
| HBP Medications                          | X  | X                                 | X  | X  | X   | X   | X   |
| Serious adverse events treatment related | X  | X                                 | X  | X  | X   | X   | X   |
| Estimated GFR CKD EPI                    |    |                                   | X  | X  | X   | X   | X   |
| Urine analyses                           | X  | X                                 | X  | X  | X   | X   | X   |
| Blood sample b                | X  | X                                 | X  | X  | X   | X   | X   |
| PLA2R1-Ab                                | X  | X                                 | X  | X  | X   | X   | X   |
| Epitope Profile                          | X  | X                                 | X  | X  | X   | X   | X   |
| Residual Rituximabemia                   |    | X                                 | X  | X  | X   |     |     |
| Rituximab-Ab                             | X  | X                                 | X  | X  | X   |     |     |
| Cytokine profile                         | X  | X At first remission a |    |    |     |     |     |
| B and T cells count                      | X  | X                                 | X  | X  | X   | X   | X   |
| End of study                             |    |                                   |    |    |     |     | X   |

a:If the sample cannot be collected at the visit when the remission is confirmed, it must be collected at the following visit.

b: urea, creatinine, electrolytes (sodium, potassium, chloride, bicarbonate), protein, albumin, full blood count.

